### Estimate the costs linked to the assessment of drug efficacy by Kato-Katz thick smear, Mini-FLOTAC and FECPAK^G2^

The mean time to process and examine one stool sample will be calculated for each separate egg counting method. We will also calculate the mean time needed to enter the demographic data and test results of a single subject, and the time to analyze and report the data. To reach an estimation of the total cost associated per sample, we will combine these data with the estimation of the costs of the raw materials and labour time needed to analyze a sample by each of the different methods. To calculate the costs for analysing samples a fixed rate will be used. Finally, a one-way sensitivity analysis will be performed to assess the impact of each parameter on the total cost for each diagnostic method separately.

### Provide proof-of-principle for qPCR to assess infection intensity and drug efficacy by means of reduction in GE

The efficacy of a single oral dose of 400 mg ALB will be reported separately for *A*. *lumbricoides*, *T*. *trichiura* and hookworms by means of genome equivalent reduction rate (GERR), using the formula below: GERR = 100% x (arithmetic mean(GE at baseline)–arithmetic mean (GE at follow-up)) / (arithmetic mean (GE at baseline)).

The corresponding 95% CI for GERR will be determined by bootstrap analysis (10,000 iterations). A permutation test will be used to assess the equivalence in drug efficacy between a duplicate Kato-Katz thick smear by means of ERR and qPCR by means of GERR for each of the STH species separately. The same level of equivalence will be applied as described in section 4.8.1. In addition, the agreement between a duplicate Kato-Katz thick smear and qPCR in the assignment of drug efficacy into ‘satisfactory’, ‘doubtful’ and ‘reduced’ will be evaluated by κ_Fleiss_ statistic.

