### General design of the field trials

A series of drug efficacy trials will be performed in four STH endemic countries (Brazil, Ethiopia, Lao PDR and Tanzania). These trials will be designed to assess the efficacy of a single oral dose of 400 mg ALB against STH infections in SAC by a variety of stool-based diagnostic methods. At the start of each trial, schools will be visited by the local principal investigator (PI) and a team of field officers, who will explain the planned trial and sampling method to the parents and teachers and the children. At baseline, SAC will be asked to provide a fresh stool sample. All children that meet all inclusion criteria and none of the exclusion criteria (see Table 1) will be enrolled in the study. They will be treated with a single oral dose of 400 mg ALB under supervision. The ALB to be used in the different studies is manufactured by GlaxoSmithKline and donated to WHO and originates from the same production batch (Batch Nr: 335726). All collected stool samples will be processed to determine the fecal egg counts (FECs; expressed in eggs per gram of stool (EPG)) for each STH using Kato-Katz thick smear (single and duplicate), Mini-FLOTAC and FECPAK^G2^. During baseline evaluation, only stool samples found to contain at least 13 eggs on duplicate Kato-Katz or at least 15 eggs on Mini-FLOTAC for at least one of the three STHs will be preserved for further molecular analysis. Fourteen to 21 days after drug administration, a second stool sample will be collected from all the children that were excreting eggs of any STH at baseline based on Kato-Katz thick smear and Mini-FLOTAC. Stool samples will be examined by Kato-Katz thick smear (single and duplicate), Mini-FLOTAC and FECPAK^G2^. All follow-up samples will be preserved for further molecular analysis. To gain insights into the operational costs for assessing drug efficacy, the time to process stool with Kato-Katz thick smear, Mini-FLOTAC and FECPAK^G2^, and the time needed to enter data and to draft reports will be assessed. The different steps of the trials are schematized in Fig 1.

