### Sample size calculation

A sample size was calculated to test the alternative hypothesis that FECPAK^G2^, Mini-FLOTAC and single Kato-Katz thick smear provide equivalent drug efficacy results measured by ERRs compared to a duplicate Kato-Katz thick smear. Given the differences in drug efficacy of ALB across the STH species [15, 21] (*Ascaris*: ~99%, hookworms: ~96%, *Trichuris*: ~65%), a level of equivalence that is acceptable for *Trichuris* may not be acceptable for *Ascaris*. Therefore, a species-specific level of equivalence was used. For *Ascaris* the level of equivalence was set at 2.5-point percentage, for hookworms and *Trichuris* the level of equivalence was set at 5.0 and 10 point percentage, respectively. Both type I and II errors were set at 0.05.

To calculate the corresponding sample size for each of the STH species, we performed a simulation study. This simulation study considered (i) variation in ERR and baseline FECs across and within STH species, (ii) variation in FECs introduced by the egg counting process, (iii) the paired ERR results across egg count methods, and (iv) a post-hoc correction for a pair-wise comparison. Based on the simulation, at least 110, 100 and 12 complete cases are required for *Trichuris*, hookworm and *Ascaris*, respectively. A detailed description of the sample size calculation is available in the supplementary information (S1 Info).

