#### qPCR

All DNA extracts will be analyzed for the presence of *A*. *lumbricoides*, *T*. *trichiura*, *N*. *americanus* and *A*. *duodenale* DNA using qPCR assays previously described [37, 63, 64]. S9 Info provides a detailed SOP on how we will perform the qPCR. The output of the qPCR analysis will be expressed in genome equivalents (GE) per ml DNA extract.

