### Assessment of the equivalence of egg reduction rates measured by Kato-Katz thick smear, Mini-FLOTAC and FECPAK^G2^

We will report the efficacy of a single oral dose of 400 mg ALB separately for *A*. *lumbricoides*, *T*. *trichiura* and hookworms, and for each FEC method by means of ERR, using the formula below:ERR=100%×(arithmeticmean(FECatbaseline)−arithmeticmean(FECatfollow-up))/(arithmeticmean(FECatbaseline))

A bootstrap analysis will be used to determine the corresponding 95% confidence intervals (95% CI) for each egg counting method and for the pair-wise differences in ERR across diagnostic methods. A permutation test will be used to assess the equivalence in ERR between a duplicate Kato-Katz thick smear, and a single Kato-Katz thick smear, Mini-FLOTAC and FECPAK^G2^. Tukey’s method will be applied for multiple comparison between methods. In addition, the agreement between a duplicate Kato-Katz thick smear and the other egg counting methods in the assignment of drug efficacy into ‘satisfactory’, ‘doubtful’ and ‘reduced’ will be evaluated by Fleiss’ kappa statistic (κ_Fleiss_). This classification of the drug efficacy will be based on the criteria recently proposed by the WHO (Table 4) [27]. The value of this statistic indicates a slight (κ_Fleiss_ <0.2), fair (0.2 ≤ κ_Fleiss_ <0.4), moderate (0.4 ≤ κ_Fleiss_ <0.6), substantial (0.6 ≤ κ_Fleiss_ <0.8) and an almost perfect agreement (κ_Fleiss_ ≥ 0.8).

**Table 4 pntd.0006912.t004:** Classification of the efficacy of a single oral dose 400 mg albendazole against STH.

STH	Satisfactory	Doubtful	Reduced
***Ascaris***	ERR ≥ 95%	85% ≤ ERR < 95%	ERR < 85%
***Trichuris***	ERR ≥ 50%	40% ≤ ERR < 50%	ERR < 40%
**Hookworms**	ERR ≥ 90%	80% ≤ ERR < 90%	ERR < 80%

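### The ERR versus GERR comparison rests on a permutation test with no stated scaling; on unscaled values it would have almost no power if GE values are several-fold larger than EPG

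*Protocol article*

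**What the plan says.** The qPCR proof-of-principle section reports efficacy "by means of genome equivalent reduction rate (GERR), using the formula below", that is, one minus the ratio of arithmetic mean GE at follow-up to that at baseline. ERR has the same form, with egg counts. On uncertainty the section says "The corresponding 95% CI for GERR will be determined by bootstrap analysis (10,000 iterations", an interval for GERR alone. For the comparison with Kato-Katz it says "A permutation test will be used to assess the equivalence in drug efficacy between a duplicate Kato-Katz thick smear by means of ERR and qPCR", using the same equivalence margins as for the egg-count methods. Agreement in the three WHO efficacy classes is also assessed, by kappa.

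The units differ. The general design section expresses Kato-Katz results in EPG, and the qPCR section says "The output of the qPCR analysis will be expressed in genome equivalents (GE) per ml DNA extract".

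The section on equivalence of ERRs between egg-count methods goes further: its bootstrap intervals are planned for each method and also "for the pair-wise differences in ERR across diagnostic methods". The qPCR section has no counterpart for GERR minus ERR.

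The margins stand under Sample size calculation: 2.5 points for Ascaris, 5 for hookworm and 10 for Trichuris. That calculation took account of "the paired ERR results across egg count methods".

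**The concern.** ERR and GERR are each a single number per species, so a permutation test of their difference has to exchange something at child level. The usual form swaps the method labels on each child's values. That is justified only if, under the null, a child's Kato-Katz values and GE values could have changed places. Equal reduction rates do not ensure this, because a rate is unit-free and its inputs are not.

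Once larger-unit and smaller-unit values are mixed, each permuted rate is driven by the children who contribute the larger-unit values. The two permuted rates then describe two different halves of the sample. Differences between children, which the paired design should cancel, enter the reference distribution and widen it.

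At stake is whether the comparison can show that qPCR gives a different efficacy result from Kato-Katz. Proof-of-principle for qPCR is one of the study's specific objectives.

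**Working it through.** **The plan's own figure.** There is none for this comparison. The 110, 100 and 12 complete cases were derived for the egg-count methods by a simulation whose inputs are in a supplement not shown, so they cannot be reproduced. They serve below only as sample sizes.

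**Mechanism, exactly.** Take two children with equal baselines *m* (EPG) and *rm* (GE), where *r* is the GE:EPG ratio. Let the fractions remaining at follow-up be *s1* and *s2*, the same by both methods, so that ERR = GERR. Swap the labels for child 1 only:

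- Set A (child 1 GE, child 2 EPG): rate = 1 - (*r s1* + *s2*)/(*r* + 1)
- Set B (child 1 EPG, child 2 GE): rate = 1 - (*s1* + *r s2*)/(*r* + 1)
- A minus B = (*s2* - *s1*)(*r* - 1)/(*r* + 1)

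The multiplier (*r* - 1)/(*r* + 1) is 0 at *r* = 1, 9/11 = 0.82 at *r* = 10 and 99/101 = 0.98 at *r* = 100. So with no difference between methods, the permuted difference carries nearly the whole difference between children. Dividing each method by its own baseline mean sets *r* to 1 and removes it.

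**Effect on the critical value.** Simulation with log-normal intensity and response, 110 children, ERR 65%, ratio 100 and no true difference: the SD of the permuted difference was 15.6 points, against a true SD of 8.9. Approximate two-sided 5% critical values are 1.96 × 15.6 = 30.6 points and 1.96 × 8.9 = 17.4 points. For a true gap of 15 points, rough power is P(Z > (30.6 - 15)/8.9) = P(Z > 1.75) = 4%, against P(Z > (17.4 - 15)/8.9) = P(Z > 0.27) = 39%. The simulated values were 2% (unscaled swap), 44% (scaled swap) and 54% (paired bootstrap). At equal units, unscaled and scaled swaps both gave 44%. At a ratio of 1/1000 the three figures were 22%, 42% and 52%.

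**Second set of assumptions.** Gamma baseline with mean 500 EPG and shape 0.5 or 1; beta-distributed survival; Poisson duplicate Kato-Katz counts times 12; log-normal qPCR error with CV 0.5 or 1; 300 data sets with 299 permutations or resamples each. Power at a true gap equal to the margin:

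| Species, n, gap | GE:EPG | Unscaled within-child swap | Scaled within-child swap | Paired bootstrap |
|---|---|---|---|---|
| Trichuris, 110, 10 points | 10-1000 | 0-2% | 15-70% | 24-75% |
| Trichuris, 110, 10 points | 1 | 17-65% | 14-67% | not compared |
| Hookworm, 100, 5 points | 10-1000 | 0-9% | 60-99% | 72-99% |
| Hookworm, 100, 5 points | 1 | 61-99% | 59-99% | 74-99% |

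Shuffling unscaled pairs freely across children did no better at ratios 10 to 1000 (0-2% and 0-10%). For hookworm it lost power even at ratio 1 (22-67%).

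With no true difference, rejection was 0-3% for the unscaled swap at ratios 10 to 1000, 2-7% for the scaled swap and 5-11% for the percentile bootstrap. At a gap of twice the margin, the unscaled swap's power ranged from 0% to 76%.

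**Smaller ratios.** A further simulation covered ratios from 3 to 1000. The unscaled swap had 0-7% power for Trichuris (gap of 10 or 15 points) and 0% for hookworm at the margin. The scaled swap had 26-54% and 72-81%, the paired bootstrap 37-64% and 87-94%. At ratios of 1 or below, Trichuris showed little or no loss. With the 1/1000 result above, this means that the size of any loss below 1 depends on the assumptions. Ascaris (n = 12) was not simulated.

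**The case against.** The strongest reply is that the article does not describe the procedure criticised. It names a permutation test and leaves open what is exchanged, and that detail normally belongs in an analysis plan. A baseline-scaled, within-child permutation fits the text. The Intensity of infection section even suggests that the authors saw the unit problem: egg-count methods are compared by correlation and by differences in counts, qPCR against Kato-Katz by correlation only.

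This stands as far as it goes. A reader might infer that the plan swaps raw GE and EPG values and discards pairing; the text supports neither. What remains is that the article fixes the type of test, states no scaling, and does not carry over to qPCR the difference interval it already plans for egg-count methods. The better analysis is thus absent from the comparison that needs it most.

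Two other extensions fail. The pairing in the sample size section concerns egg-count methods; it did not size ERR against GERR. And the egg-count equivalence section needs no change: those methods share EPG units and already have an interval for the difference.

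It is also fair that GERR with its interval, the kappa agreement and the GE-to-egg-count correlation will be reported whatever the p-value. None of them is an inference on the difference in rates.

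**Conclusion.** The point holds conditionally. If labels are swapped on unscaled values and GE is several-fold larger than EPG, the test has almost no power at the margin, while a scaled or paired analysis of the same data has far more. The condition on the ratio is an assumption, since the documents give none.

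Three stronger readings are not supported:

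- That the test produces false positives. The fault is conservatism: rejection under no difference falls to 0-3%.
- That power is always negligible. It is not at a ratio near 1, and it recovers for larger gaps under some assumptions.
- That qPCR will be wrongly endorsed. That follows only if a non-significant difference is read as equivalence. In a test against the margin, an over-wide reference distribution would instead make true equivalence harder to show.

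The remedy does not solve everything. At 110 children, even the better methods have only moderate power against a 10-point Trichuris gap under the noisier assumptions.

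**What to change.** In the qPCR proof-of-principle section, extend the bootstrap planned for egg-count differences to GERR minus ERR. Resample whole children, keeping each child's baseline and follow-up Kato-Katz and GE values together. Report the interval, preferably BCa because the percentile interval is slightly liberal, and declare equivalence only if it lies within the species margin. Point to the margins under Sample size calculation, since the section number now cited does not appear in the article.

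If a permutation test is kept, state that each method's values are first divided by that method's own baseline mean and that methods are swapped only within child.

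The cost is a sentence or two of text and a few lines of code, with no new data.

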### Assess associations between frequency of SNPs linked to BZ resistance measured by pyrosequencing and history of drug pressure and drug efficacy

To assess the association between mutant SNPs linked to BZ resistance and history of drug pressure, a permutation test will be applied to evaluate differences in frequency of mutant SNPs linked to BZ in the baseline samples across the study sites. Tukey’s method will be applied for pair-wise comparisons between the study sites.

To assess the association between mutant SNPs linked to BZ resistance and drug efficacy, a permutation test will be applied to evaluate any difference in frequency of mutant SNPs linked to BZ across the four levels of individual response to ALB (Table 3). Tukey’s method will be applied for pair-wise comparisons between the four levels of individual response.

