**Methods:**

A series of drug efficacy trials will be performed in four STH endemic countries with varying drug pressure (Ethiopia and Brazil: low drug pressure, Lao PDR: moderate drug pressure and Tanzania: high drug pressure). These trials are designed to assess the efficacy of a single oral dose of 400 mg albendazole (ALB) against STH infections in school-aged children (SAC) by microscopic (duplicate Kato-Katz thick smear, Mini-FLOTAC and FECPAK^G2^) and molecular stool-based diagnostic methods (quantitative PCR (qPCR)). Data will be collected on the cost of the materials used, as well as the time required to prepare and examine stool samples for the different diagnostic methods. Following qPCR, DNA samples will also be submitted for pyrosequencing to assess the presence and prevalence of single nucleotide polymorphisms (SNPs) in the β-tubulin gene. These SNPs are known to be linked to AR in animal STHs.

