**Discussion:**

The results obtained by these trials will provide robust evidence regarding the cost-efficiency and diagnostic performance of the different stool-based diagnostic methods for the assessment of drug efficacy in control programs. The assessment of associations between the frequency of SNPs in the β-tubulin gene and the history of drug pressure and drug efficacy will allow the validation of these SNPs as a marker for AR in human STHs.

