### Study population

The study will focus on SAC (age 5–14) since they are the major target of PC programs targeting STH, and they usually represent the group with highest worm burdens for *A*. *lumbricoides* and *T*. *trichiura* [56]. This study will be conducted in Ethiopia, Tanzania, Lao PDR and Brazil. The selection of these sites is based on their experience in assessing drug efficacy [13, 15], evaluating the performance of diagnostic methods [57–59] and the availability of well-equipped diagnostic facilities and skilled personnel, and PC history (Table 2).

**Table 2 pntd.0006912.t002:** An overview of the countries, study sites and institutions involved in work package 1 of the Starworms project as well as their respective drug pressure and the type of benzimidazole drug administered.

Country	Study site	Institution	Drug Pressure *	Drug
**Brazil**	Americaniñas, Belo Horizonte	Fiocruz—Research institute of Renê Rachou	Low	ALB
**Ethiopia**	Jimma Town, Jimma Zone	Jimma University	Low	ALB
**Lao PDR**	Nam Bak, Luang Prabang	National institute of public health	Medium	MEB
**Tanzania**	Chake Chake, Pemba	Public Health Laboratory—Ivo de Carneri	High	ALB

* The classification of the countries into the four levels of drug pressure was based on the reported national coverage of drug administration to preschool (preSAC) and school aged children (SAC) for the last 5 years (2009–2014; Preventive Chemotherapy Database of the WHO). Very high drug pressure: coverage >80% for preSAC and SAC for each of the last 5 years; moderately high: coverage >50% for preSAC and/or SAC for each of the last 5 years; moderate: coverage >30% for preSAC or SAC for each of the last 5 years; low: coverage is <30% for both preSAC and SAC for each of the last 5 years.

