#### Pyrosequencing

In two subsets of the DNA samples, we will apply a previously described pyrosequencing protocol [30, 52] to determine frequency of mutant SNPs in the three codons of the ß-tubulin associated with BZ resistance. The first subset will consist only of baseline DNA samples, and will be used to assess the association between drug pressure history and the corresponding frequency of mutant SNPs linked to BZ resistance. Per study site, 60 baseline DNA samples positive for each STH species (*Ascaris*, *Trichuris* and hookworm) will be randomly selected from the available baseline DNA samples. To avoid these samples representing one school or one level of individual response to ALB, selection of the samples will be proportionately to the total number of cases per school and individual drug response (Table 3).

**Table 3 pntd.0006912.t003:** Classification of the individual response to a single oral dose 400 mg ALB against STH based on the individual egg reduction rate (iERR).

STH	Cured	Responder	Poor responder	Non-responder
***Ascaris***	iERR = 100%	iERR ≥ 95%	85% ≤ iERR < 95%	iERR < 85%
***Trichuris***	iERR = 100%	iERR ≥ 50%	40% ≤ iERR < 50%	iERR < 40%
**Hookworms**	iERR = 100%	iERR ≥ 90%	80% ≤ iERR < 90%	iERR < 80%

We will use a second set of DNA samples to assess the association between individual responses to ALB by pyrosequencing the ß-tubulin gene. At each site, samples from at least 30 participants who were cured (baseline samples only) and from at least 30 participants who were still excreting eggs at follow-up (both baseline and follow-up samples) will be selected for each STH species separately. Participants which still excreted eggs will be stratified, into ‘responders’, ‘poor responders’ and ‘non-responders’. This stratification will be based on WHO thresholds used for classifying the efficacy into ‘satisfactory’ (‘responders’), ‘doubtful’ (‘poor responders’) and ‘reduced’ (‘non-responders’) [27] (Table 3). A total of 10 participants will be randomly selected for each stratum. Total DNA will be extracted from these stool samples and sent for pyrosequencing at McGill University (Canada).

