By standardizing the drug efficacy trials (e.g., egg count method, follow-up period, anthelmintic drug and statistical analysis) and strategically selecting the study sites (varying drug pressure history, and hence possibly differences in drug efficacy), we hope to provide complementary insights into SNPs in the β-tubulin gene as a marker for BZ resistance in human STHs. If these SNPs play a role in AR, we expect an increase in frequency in mutant SNPs in STHs as a function of increased drug pressure history and decreased individual response to treatment. However, this molecular part of the study may face some challenges, which may impede a straightforward interpretation of the results. First, if the expected trends in SNPs are not detected, it is not possible to completely exclude them as a marker for BZ resistance. Furthermore, it could also indicate that resistance to BZ has not yet emerged, which would also jeopardize any downstream objectives (e.g. comparison of pyrosequencing and LAMP for the assessment of SNPs linked to BZ resistance and assessing pooling samples as a cost-saving strategy to determine the frequency of SNPs linked to BZ resistance). It is also important to note that any observed trends would only suggest an association rather than causal relationship. Second, it remains unclear whether we will be able to select the number of cases per level of individual response for each of the different STH species. Finally, the classification of the individual response is based on the outcome of imperfect tests (sub-optimal sensitivity), further complicating the interpretation.

To conclude, the combined results of this study are expected to answer a number of outstanding questions with regards to how to best monitor drug efficacy and measure AR in populations that are being subjected to PC for STH infections. The results could be translated into novel recommendations for the scientific community on what is the best diagnostic method to assess drug efficacy in ongoing control programs and will create the basis to set up a robust surveillance system.

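### The SNP-versus-drug-pressure test is an unordered comparison of four sites, so it cannot separate drug pressure from site, and the drug-pressure part of the marker validation is unsupported

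*Protocol article*

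**What the plan says.** The objective is to assess associations of SNP frequency with drug-pressure history and with drug efficacy.

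- **Exposure.** The abstract (Methods) gives the levels as "Ethiopia and Brazil: low drug pressure, Lao PDR: moderate drug pressure and Tanzania: high drug pressure". The footnote to Table 2 (Study population) says: "The classification of the countries into the four levels of drug pressure was based on the reported national coverage of drug administration". Every child at a site therefore carries the same value.
- **Data.** Under Pyrosequencing, each site contributes "60 baseline DNA samples positive for each STH species", and "selection of the samples will be proportionately to the total number of cases per school and individual drug response".
- **Test.** The analysis section on SNP associations words its test as follows: "permutation test will be applied to evaluate differences in frequency of mutant SNPs linked to BZ in the baseline samples across the study sites". Pairs of sites are then compared by Tukey's method. A second paragraph plans a separate permutation test across four levels of individual response to albendazole.
- **Expectation and claim.** The main Discussion states the predicted direction: "we expect an increase in frequency in mutant SNPs in STHs as a function of increased drug pressure history", and likewise with poorer individual response. It adds that a trend would show association, not cause. The abstract (Discussion) says that assessing both associations "will allow the validation of these SNPs as a marker for AR in human STHs".

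**The concern.** The question concerns drug pressure, but the test concerns sites. The level of pressure is not used, no trend is tested, and the two low-pressure sites are separate groups. A difference between Brazil and Ethiopia alone, which share a pressure category, would give a significant result under an analysis labelled as association with drug pressure.

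Sampling 60 children per site makes the site means precise but adds no exposure units: there are four, two of them tied. Sites also differ in other ways. For example, Table 2 lists mebendazole for Lao PDR, the only medium-pressure site, and albendazole for the other three. Ordinary geographic variation in allele frequency could then be read as evidence on pressure and carried into the validation claim.

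**Working it through.** The document states no sample size rationale, power or alpha for this test, so there is no figure to reproduce. The 110, 100 and 12 complete cases belong to the egg-reduction-rate equivalence objective.

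**Inputs**

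- k = 4 sites: two low, one medium, one high (abstract Methods; Table 2).
- n = 60 samples per site and species (Pyrosequencing), so 4 × 60 = 240 per species.
- Alpha 0.05: stated only for the equivalence objective, assumed here.
- rho, the share of SNP-frequency variance between sites for reasons other than pressure: not in the document, assumed 0 to 0.20.
- Unit of permutation: not stated. Individual samples is the natural reading.

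**1. Rejection by the across-site test with no pressure effect**

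A one-way comparison is used as a proxy. With F(3, 236), the critical value is 2.643. Between-site variance inflates the statistic by 1 + 60·rho/(1 − rho), so

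P(reject) = P[F(3, 236) > 2.643 / (1 + 60·rho/(1 − rho))].

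| rho | inflation | P(reject) |
|---|---|---|
| 0 | 1.00 | 5% |
| 0.01 | 1.61 | 18% |
| 0.02 | 2.22 | 32% |
| 0.05 | 4.16 | 59% |
| 0.10 | 7.67 | 79% |
| 0.20 | 16.0 | 92% |

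The same calculation for the two low-pressure sites alone, unadjusted, on F(1, 118), gives 12%, 33% and 48% at rho 0.01, 0.05 and 0.10.

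As a check, an actual permutation test was run on skewed frequencies with an assumed mean near 10% (2,000 runs). It rejected in 4% with no site variation. It rejected in 24%, 61% and 83% when the 95% range of site means was 7–14%, 5–20% and 3–27%.

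**2. Rejection together with the expected order**

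Of 4! = 24 orderings of the site means, 2 have both low sites below medium below high: 2/24 = 8.3%. With no pressure effect the sites are exchangeable, so the joint probability is P(reject)/12:

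- rho 0.01: 18%/12 = 1.5%.
- rho 0.20: 92%/12 = 7.7%.

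The permutation runs with site variation gave 2% to 7%.

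**3. The site as the unit**

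- Permuting the labels low, low, medium, high gives 4!/2! = 12 arrangements, so the smallest p-value is 1/12 = 0.083.
- A linear trend on four site means has 2 df and a critical t of 4.303. It needs |r| ≥ 4.303/√(4.303² + 2) = 0.95.
- Counting 240 samples as independent (238 df, t = 1.970), it would need only |r| ≥ 1.970/√(1.970² + 238) = 0.13.

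**The case against.** Several points on the other side are fair.

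- **Direction is fixed in advance.** The Discussion predicts a rise with pressure, and the Tukey pairs would show whether the sites follow it. This stands in part. A reader who demands both significance and the right order would be misled in about 1% to 8% of studies, not 18% to 92%. But the analysis section states no such rule, and the Tukey comparisons also treat samples as the units.
- **Validation has a second leg.** A reader might infer that the whole marker validation is unsupported. The document does not bear that out. The abstract also relies on drug efficacy, and the individual-response comparison draws samples at every site. Two limits remain: that comparison is not said to be stratified by site, and the Discussion doubts that the response strata will fill.
- **Confounding is not total.** A reader might infer that pressure is fully tied to continent or to drug. Ethiopia (low) and Tanzania (high) share a continent, and the Introduction treats albendazole and mebendazole as one class with one mode of action.
- **p < 0.05 is not impossible in principle.** The floor of 0.083 applies to a permutation of site labels; a site-level trend could pass 0.05 with |r| above 0.95.
- **The unit of permutation is unstated.** True, but a site-label permutation could not reach 0.05, so the test does not serve its purpose on either reading.
- **Association, not causation, is conceded.** That is a different limit. Here even association with pressure, as distinct from site, cannot be isolated, and the Discussion does not say so.

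**Conclusion.** The point holds for the drug-pressure half of the SNP objective. The planned test detects site differences of any kind and in any order; with one pressure value per site and four sites, a significant result cannot be attributed to drug pressure. That part of the validation claim in the abstract is unsupported.

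With a between-site variance share of 0.01 to 0.20 unrelated to pressure, the test rejects in about 18% to 92% of studies. These are omnibus rejections when sites truly differ, not rates of a false pressure gradient; rejection in the expected order is about 1% to 8%. Both ranges rest on the assumed variance share and on alpha 0.05. With no site variation the test holds its 5%. The count of 12 arrangements and the floor of 0.083 follow from the design alone.

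The level names in Table 2 (Medium, High) do not match those in its footnote. That is a separate editorial matter and does not bear on this conclusion, since the labels do not enter the test.

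**What to change.** 1. Report SNP frequency by site and species with confidence intervals, descriptively, in the pre-stated order low, low, medium, high. Declare that n = 4 sites and that site and pressure cannot be separated.
2. State that the across-site permutation p-value and the Tukey site comparisons will not be read as evidence on drug pressure.
3. Rest inference on the individual-response comparison, with permutation stratified by site.
4. In the abstract, replace validation by exploratory evidence as far as drug pressure is concerned, and add the four-site limit to the Discussion.

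This needs no new samples or assays, only changes to the analysis text and the claim. The cost is a weaker stated conclusion for half of the objective.
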